### Assessments

3.5

#### Sociodemographic and medical information

3.5.1

Sociodemographic and clinical data will be collected through a customized survey directed to the caregivers. The variables include age, sex assigned at birth, socioeconomic position, medication use, and general health status. Age will be recorded in years and months, calculated as the time elapsed from birth to the date of the first interview with the field researchers.

The socioeconomic position of children will be evaluated using a previously described instrument (28). Briefly, the instrument evaluates six dimensions: (i) Housing characteristics; (ii) access to technology; (iii) possession of material goods; (iv) consumption habits; (v) level of education of the head of the household; and (vi) household income. The sum of the scores for all questions ranges from 0 to 1000. According to this score, households are classified into five socioeconomic groups: A (>845), high; B (>696 and ≤ 845), upper-middle; C+ (>535 and ≤ 696), middle; C− (>316 and ≤535), lower-middle; and D (≤316), low.

#### Neuropsychological assessment

3.5.2

All participants will be screened with age-appropriate instruments. Children under 4 years will be assessed using the POSI (29), those aged 4–11 years with the AQ-10 child version, and those 12 years and older with the AQ-10 adolescent version (30). Additionally, children in Group A will undergo a formal evaluation of autism symptom severity using the Spanish version of the Childhood Autism Rating Scale (CARS) (31, 32).

##### Parent’s observations of social interactions

3.5.2.1

POSI is a screening tool for neurotypical children aged 16 to 48 months, administered to parents or immediate caregivers. The reported internal consistency is high (α = 0.83), with a sensitivity of 89% and a specificity of 54% (29). This instrument is a brief (7-item) questionnaire based on parental observations of social interactions, the purpose of which is to identify possible signs of autism. Each item is scored as a 0 or 1; a total score of 3 or higher indicates autistic traits.

##### 10-item autism spectrum quotient

3.5.2.2

The AQ-10 is a screening tool designed to measure autistic associated traits. There are adapted versions for different age groups; for this research, the child version, for ages 4 to 11, and the adolescent version, for ages 12 and up, will be used (31). The original AQ consists of 50 questions, but we will use an abbreviated version consisting of 10 items. AQ-10 evaluates various areas, including interpersonal relationships, social skills, and communication. AQ-10 scores range from 0 to 10 points, with scores of 6 and above indicating autistic traits. In the validation study by Allison et al. (2012), the AQ-10 child version showed a sensitivity of 95% and a specificity of 97%, while the AQ-10 adolescent version showed a sensitivity of 93% and a specificity of 95% for the ≥ 6 cutoff.

##### Childhood autism rating scale

3.5.2.3

CARS will be administered only to autistic children (Group B) to evaluate the severity of autistic symptoms. This scale is a diagnostic observational assessment that has consistently demonstrated strong psychometric properties. In the original validity study, the internal consistency was exceedingly high (Cronbach’s alpha α = .94) (33). In the Spanish version, the evaluator assigns a score from 1 to 4 in each of the 15 areas included (31, 32). A score of 1 is given when age-appropriate behavior is observed, while a score of 4 is given when the observed behavior is at the farthest end of what is expected for the child’s age. Scores equal to or greater than 30 are indicative of autism. Specifically, scores between 30 and 36.5 are classified as mild to moderate autism, while scores equal to or greater than 37 indicate severe autism.

##### Note on screening results

3.5.2.4

If a score meets or exceeds the cutoff on any screening tool (POSI or AQ-10), parents or caregivers will be informed that the result suggests a suspicion of autism. They will be advised that these are screening instruments with the potential for false positives and negatives, and that the result does not constitute a definitive diagnosis. A confirmation by a qualified professional will be recommended.

#### Nutritional assessment

3.5.3

##### Anthropometry

3.5.3.1

Height and weight will be measured in duplicate by trained personnel applying standardized protocols. During the assessment children are barefoot and wear light clothing. Body weight will be measured using a digital scale (Seca) calibrated to the nearest 0.1 kilograms (kg). Height measured in centimeters (cm)) will be assessed using a portable stadiometer (Seca) with a precision of 1millimetre (mm). Waist circumference will be measured midway between the lowest rib margin and the iliac crest, with the children in a standing position.

A non-elastic flexible SECA measuring tape will be used for measuring circumferences. Neck circumference (measured in cm) will be measured using a non-stretchable measuring tape to the nearest 0.10 cm. The tape will be placed on the midline of the neck between the cervical backbone and the anterior neck while the children stand upright, face forward, and shoulders relaxed. Waist circumference (measured in cm) will be measured at the midpoint between the lowest border of the rib cage and the upper iliac crest to the nearest 0.1 cm. Arm circumference will be measured at a mark point in the middle of the posterior surface of the left humerus between the acromion and the olecranon process.

Abdominal obesity will be defined as having a waist circumference at or above the 90th percentile in comparison to children of similar age and sex. Percentile cut-off points for abdominal circumference will be based on the reference data from African-American, European-American, and Mexican-American children (34). Cut-off points for arm circumference will be ≥ 13.6 cm (normal), ≤ 13.5 to ≥ 11.6 cm (undernutrition), and ≤ 11.5 cm (severe undernutrition) (35). Filgueiras parameters will be used for determining malnutrition in children using neck circumference (36).

Using the World Health Organization (WHO) software Anthro and AntroPlus, we will calculate z-scores for BMI-for-age, and height-for-age. Anthro uses 2006 WHO growth reference curves (37). AntroPlus uses the 2007 WHO growth reference curves (38). The standard deviation (SD) cut-off points we will use are the following: BMI-for-age (< -2 SD, thinness; < -3 SD, severe thinness; > +1 SD, overweight; > +2 SD, obesity); height-for-age (> +2 SD, tall; +2 SD to -2 SD, normal; < -2 SD, stunting).

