#### Group A - autistic children

2.2.1

This group includes children and adolescents aged 3 to 17 years (n = 100), from diverse socioeconomic backgrounds, who have been previously diagnosed with autism by certified physicians following the Ecuadorian Clinical Practice Guide and was based on the DSM-5 criteria (23). At least 100 participants are required, but we will accept up to 150 children.

*Inclusion criteria*

Age between 3 and 17 years.Previous autism diagnosis by a neurologist or psychiatrist after meeting the DSM-5 diagnostic criteria for autism. Such diagnosis will include the following International Classification of Diseases, 10th Edition (ICD-10) categories: F84.0 (Childhood autism), F84.5 (Asperger’s syndrome), F84.8 (Other pervasive developmental disorders), and F84.9 (Pervasive developmental disorder, unspecified).

*Exclusion criteria*

Inability to sit and/or stand independently.

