#### Group B - non-autistic children without neurodevelopmental disorders

2.2.2

This group will include children and adolescents aged 3 to 17 years (n = 100), from the general population with age and gender distribution similar to the autistic group.

*Inclusion criteria*

Age between 3 and 17 years.

*Exclusion criteria*

A 10-item Autism Spectrum Quotient (AQ-10) score of 6 points or higher.A Parent’s Observations of Social Interactions (POSI) score of 3 points or higher.History of diagnosis, therapy, or treatment for any neurodevelopmental disorder coded under ICD-10 F84.Inability to sit and/or stand independently.

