#### Group C - non-autistic children with other neurodevelopmental disorders

2.2.3

This group will include children and adolescents aged 3 to 17 years (n = 100) diagnosed with intellectual, psychological, emotional, or behavioral developmental disorders not including autism.

*Inclusion criteria*

Age between 3 and 17 years.Diagnosis with psychological developmental disorders (ICD-10 F80-F89), which includes: F80 (specific developmental disorders of speech and language), F81 (specific developmental disorders of school skills), F82 (specific developmental disorder of motor function), F83 (mixed specific developmental disorders), F88 (other disorders of psychological development) and F89 (unspecified disorder of psychological development). Diagnosis with intellectual disabilities (ICD-10 F70-F79), including F70 (mild mental retardation), F71 (moderate mental retardation), F78 (other mental retardation), F79 (unspecified mental retardation). Diagnosis with emotional and behavioral disorders usually occurring in childhood and adolescence (ICD-10 F90-F98), which includes F90 (hyperkinetic disorders), F91 (conduct disorders), F92 (mixed disorders of conduct and emotions), F93 (emotional disorders with onset specific to childhood), F94 (disorders of social functioning with onset specific to childhood), F95 (tic disorders), and F98 (other emotional and behavioral disorders that commonly occur in childhood and adolescence).

*Exclusion criteria*

AQ-10 score of 6 points or higher.POSI score of 3 points or higher.Diagnosis with or report of having received therapy or treatment for a neurodevelopmental disorder coded as ICD-10 F84.Being unable to sit and/or stand autonomously.

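### Arm circumference is classified by fixed centimetre cut-offs with no stated age limit in a sample aged 3 to 17, so the category would mainly track age and be very insensitive beyond early childhood

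*Protocol article*

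**What the plan says.** Section 3.5.3.1 gives the arm-circumference rule in centimetres only: "Cut-off points for arm circumference will be ≥ 13.6 cm (normal"), then "≤ 13.5 to ≥ 11.6 cm (undernutrition), and ≤ 11.5 cm (severe undernutrition"). A source is cited. The text does not say which ages or which sex the thresholds apply to.

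The eligible age range is the same in every group:

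- Section 2.2.1: "This group includes children and adolescents aged 3 to 17 years (n = 100")
- Section 2.2.2: "This group will include children and adolescents aged 3 to 17 years (n = 100), from the general population"
- Section 2.2.3: "This group will include children and adolescents aged 3 to 17 years (n = 100) diagnosed with" other developmental disorders

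Other measures in section 3.5.3.1 are referenced to age. Abdominal obesity is a waist circumference "at or above the 90th percentile in comparison to children of similar age and sex". BMI and height are converted to WHO z-scores for age, with thinness and stunting both set below −2 SD. Section 4.2 (Study limitations) adds that the instruments were chosen to suit developmental stage and that age will be a covariate in the multivariate models.

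**The concern.** A fixed centimetre threshold has a stable meaning only if the measured quantity is roughly constant over the ages it covers. Arm circumference is not constant from 3 to 17 years. A boundary that falls in the lower part of the distribution for a 3-year-old falls far out in the tail for an adolescent. Followed as printed, the rule would put nearly all older children in the normal category whatever their nutritional state, and most positives would come from the youngest.

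Comparing nutritional status is the first specific aim in the Introduction, and the arm category is one of the indices that describe it. A low count of undernutrition on this index could be read as a finding about the children when it is a property of the threshold. If two groups differ in age mix, part of that difference would show up as a difference in undernutrition.

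**Working it through.** **1. Is the sample size affected?** Section 2.2.4 uses p1 = 0.57, p2 = 0.37, and z-values 1.96 and 0.84.

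n = (1.96 + 0.84)² × [0.57 × 0.43 + 0.37 × 0.63] / 0.20² = 7.84 × 0.4782 / 0.04 = 93.7, which rounds up to 94, the plan's figure. Allowing for 5% non-response, 94 / 0.95 = 98.9, or 99; the plan rounds to 100. The two proportions are built from overweight/obesity and thinness/underweight prevalences. Arm circumference does not enter.

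**2. Adolescent illustration.** The documents give no distribution of arm circumference, so the means and SD here are assumptions. Take SD 3 cm and a mean of 25 cm (range 22 to 28), with z = (13.5 − mean) / 3.

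| Assumed mean (cm) | z | Share flagged |
|---|---|---|
| 22 | −2.83 | 0.23% |
| 25 | −3.83 | about 0.006% |
| 28 | −4.83 | under 0.001% |

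A −2 SD rule, the one used for BMI-for-age in the same section, corresponds to 2.3% of a normal distribution.

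**3. Illustration across the whole age range.** This is also on assumed values. The median rises linearly from 15–16.5 cm at age 3 to 22–28 cm at age 17, the coefficient of variation (CV) is 8% to 12%, and ages are spread evenly over 15 year-bands. The boundary is placed at 13.55 cm, between the two printed limits, and z = (13.55 − median) / (CV × median). The pairs of medians used were 15→22, 15.5→24, 16→26 and 16.5→28 cm, each with CV 8%, 10% and 12%.

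| Age | Distance of the boundary below the median, range over the 12 scenarios |
|---|---|
| 3 | 0.8 to 2.2 SD |
| 8 | 1.9 to 4.3 SD |
| 11 | 2.4 to 5.2 SD |
| 17 | 3.2 to 6.5 SD |

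Worked example (16→26 cm, CV 10%): at age 3, (13.55 − 16) / 1.6 = −1.5; at age 17, (13.55 − 26) / 2.6 = −4.8.

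Take children below −2 SD for their age as the target. The share of them flagged at a given age is Φ(z) / Φ(−2), capped at 1. Over the scenarios:

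- The average share flagged over all ages is 5% to 56%.
- Fewer than half are flagged in 7 to 14 of the 15 age-years, and in 9 or more in every scenario but the most favourable one.
- Ages 3 to 5 are 3 of the 15 bands (20%) but supply 70% to 99% of all flags.

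The most favourable scenario (15→22 cm, CV 12%) shows the age dependence well. At age 3, z = (13.55 − 15) / 1.8 = −0.81, so about 21% of all children are flagged. At age 17, z = (13.55 − 22) / 2.64 = −3.20, so about 0.07% are flagged.

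**4. Does the age covariate repair it?** No. A covariate adjusts a comparison of the recorded categories. It cannot reclassify a child whom the threshold has already recorded as normal.

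**The case against.** The strongest reply has five parts.

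- **The text does not say the cut-offs are applied at every age.** This stands as a limit on wording. Section 3.5.3.1 cites a source and refers to a technical sheet in an annex, neither of which is available here, and the article is a condensed document. What the page supports is that no age limit is stated. But exact thresholds are printed for a sample of stated age range with nothing to restrict them, so this is a rule that is badly fixed, not a detail left for later.
- **Undernutrition is measured properly elsewhere.** This stands. BMI-for-age and height-for-age z-scores cover every age in the sample, and no section says that the arm category feeds a combined malnutrition outcome. Since nutritional status underlies the sample size, a reader might infer that the defect reaches that calculation. It does not (step 1).
- **Arm circumference may not be the only fixed threshold.** A reader might infer that it is. Section 3.5.3.1 judges neck circumference by published parameters whose form is not shown, so that cannot be claimed either way.
- **Matching and adjustment limit bias between groups.** This largely stands for Groups A and B, since sections 2.2.2 and 2.3 align Group B with Group A on age and sex, and age is a covariate. It is weaker for Group C. Section 2.2.3 states no age matching for that group, although the abstract describes all non-autistic peers as matched on age and sex. Neither feature restores lost sensitivity.
- **The size of the effect rests on assumed distributions.** This stands too. It limits how exactly the loss can be stated, but its direction is the same in every scenario tried.

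**Conclusion.** The point holds for this index. As written, the arm-circumference categories have no age or sex limit in a sample aged 3 to 17, in a section that references waist, BMI and height to age. The category would mainly track age, with very low sensitivity expected beyond early childhood. On assumed adolescent means of 22 to 28 cm with SD 3 cm, it would flag about 0.23% to under 0.001%, against 2.3% at −2 SD.

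A reader might go further and say that the rule cannot detect undernutrition in most of the sample. The documents do not support that: they give no arm-circumference distribution, and in the most favourable assumed scenario the rule still flags 56% of children below −2 SD on average over ages.

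The consequence is confined to this one index. The sample size is unaffected and the age-standardised undernutrition measures remain valid. Distortion between groups is a concern mainly in comparisons with Group C. The textual point is firm; the size of the loss depends on the assumptions shown.

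**What to change.** Reconcile the cut-offs with the age range in section 3.5.3.1, in one of two ways:

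1. Express arm circumference as an age- and sex-referenced z-score or percentile, as the section does for its other indices.
2. State the age band for which the cited reference set the centimetre categories and use them only within it. Above that band, analyse arm circumference as a continuous measure adjusted for age and sex.

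Under the second option, also state that the fixed category feeds no malnutrition outcome above the band.

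The cost is one sentence in the protocol and a reference table in the analysis code. The measurements themselves do not change, and the sample size does not need to be revisited.

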##### Bio-impedance

3.5.3.2

Body composition will be measured using bioelectrical impedance analysis (InBody). Children will stand on the InBody scale with their bare hands and feet making contact with the eight electrodes (2 palm, 2 thumb, 2 toe, and 2 heel); the measurement will take approximately 30 seconds. Body composition measurements will include: Total body fat percentage, visceral fat percentage, body water measured in liters, and muscle mass percentage. Measures will be automatically calculated by InBody (39, 40).

##### 24-hour dietary recall

3.5.3.3

Data on recent food intake will be collected using 24-HDR, a previously validated instrument on three different days (two weekdays and one weekend day) (41). Data collection will include information on the time of food consumption, type, quality and quantity of food (using home measurements), and cooking method. The foods consumed will be classified into gluten sources, casein sources, and ultra-processed foods. A single food item may be assigned to more than one category (42). Visual food models and photographs using local food albums will be used to accurately estimate the quantities of food consumed (43). Total calories, grams of protein, fat, and carbohydrate, intakes of iron, calcium, folate, vitamin C, and vitamin D will be calculated using food composition reference tables (44). The detailed food-level data obtained from the 24-hour dietary recalls will also allow us to examine dietary patterns by food groups (e.g., dairy, fruits, cereals, fish), following recent recommendations in the literature (45).

#### Neurophysiological assessment

3.5.4

Neurobehavioral assessments will be performed using a smartphone-based platform (21). The assessment will include a general measurement of spontaneous and stimulus-evoked postural, head, facial, and vocal responses, along with specific neurometric tests, including PPI and SH. During the experiment, children will use wired headphones to watch an audio-normalized video on a smartphone. The application delivers auditory stimuli, and the participant’s responses are captured using the smartphone’s front-facing camera at 60 frames per second.

Two audio-normalized videos will be used: one for younger children (aged 3–5 years), featuring a compilation of moving shapes and animals, and one for older children (aged 6 years and older), which depicts a basic storyline of a boy and a girl playing a video game. Both videos are devoid of any language content. The videos are audio-normalized by adjusting the audio track to ensure its peak level does not exceed approximately 60–70 decibels (dB).

While the participant watches the video, computer vision algorithms are used to track and record the position of the participant’s facial landmarks over time. The individual eyeblink traces will be analyzed with custom software developed in R. Eyelid position is calculated based on the tracked facial landmarks. Eyeblink traces are filtered and normalized as previously described (22). From valid normalized trials, we will extract the following three outcome measures: (i) PPI, (ii) SH, and (iii) general motor behavior.

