The initial session will involve obtaining informed consent, collecting baseline sociodemographic information, health status, treatments/therapies, and conducting the first 24-HDR. CARS and autism screening questionnaires (POSI, AQ-10) will be administered concurrently. Caregivers will receive stool collection kits with instructions; child presence is optional. During the second session, children will undergo the first neurobehavioral assessment (15–20 minutes), comprehensive anthropometric measurements, body composition evaluation, and the second 24-HDR. The third session will include another neurobehavioral assessment, the final 24-HDR, and stool sample collection. Any outstanding data will be collected in the last session.

Throughout the study, caregivers may contact researchers for clarification and will have the option to complete questionnaires remotely. All participants retain the right to withdraw at any time without penalty. Following the study’s completion, caregivers will receive individualized reports on their child’s nutritional status, along with a summary of the aggregate study results. All materials will be presented in an accessible format and in Spanish.

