##### General sensorimotor behavior

3.5.4.3

During the PPI and SH sessions, the smartphone’s front-facing camera and microphone passively capture a broad range of behavioral data, extending beyond the specific eyeblink responses required for the primary neurometric tests. Ten specific behaviors previously identified as differing between autistic and NA children will be analyzed in this study (22).

*Dependent variables:*

Task engagement: The percentage of trials in which the participant is not detectable within the smartphone’s camera frame.Headphone interaction: The percentage of trials with observed touching or adjustment of the headphones.Non-syllabic vocalizations: The frequency (percentage of trials) and total duration of non-linguistic vocal sounds.Postural stability: The degree of anteroposterior postural sway.Head movement: The percentage of trials with observed head rotation.Orofacial movement: The frequency and duration of mouth openings.Oculomotor activity: The mean amplitude of horizontal pupil movement per session.Vestibulo-ocular reflex (VOR) function: The correlation between the direction of head turns and compensatory pupil movement.Initial baseline variability: The variation in baseline (pre-stimulus) eyelid position during the first five trials of a session.Baseline stability: The change in the variability of baseline eyelid position from the start to the end of the session.

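### Taking general motor behavior only from valid normalized eyeblink trials contradicts the definition of task engagement and would set it to 0% for every child

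*Protocol article*

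**What the plan says.** Section 3.5.4 (Neurophysiological assessment) describes how the smartphone recording becomes outcomes. Computer vision tracks the child's facial landmarks during the video, and "Eyelid position is calculated based on the tracked facial landmarks". The eyeblink traces are then filtered and normalized by a method taken from a cited source. The next sentence sets the extraction rule: "From valid normalized trials, we will extract the following three outcome measures: (i) PPI, (ii) SH, and (iii) general motor behavior". General motor behavior is therefore placed under the same trial restriction as PPI and startle habituation (SH).

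Section 3.5.4.3 (General sensorimotor behavior) lists ten behaviors, selected because earlier work found that they differ between autistic and non-autistic children. The first is "Task engagement: The percentage of trials in which the participant is not detectable within the smartphone’s camera frame". Another is "Head movement: The percentage of trials with observed head rotation". The same section says that the camera and microphone "passively capture a broad range of behavioral data, extending beyond the specific eyeblink responses required for the primary neurometric tests".

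Sections 3.5.4.1 and 3.5.4.2 give the session lengths: 44 trials for PPI and 22 for SH, each including two practice trials.

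**The concern.** The extraction rule selects trials on a condition that the outcome itself violates. Task engagement counts trials in which the face is lost, while the rule keeps only trials in which the face was tracked well enough to yield a normalized eyelid trace. The two statements cannot both be applied.

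The third objective in the Introduction compares sensorimotor profiles between autistic children and their peers. It names PPI and SH, and section 3.5.4 makes general motor behavior the third outcome of the same assessment. The fourth objective relates sensorimotor differences to symptom severity. An outcome that is constant across all children can inform neither. If the analyst notices this only at extraction, the choice of which trials to count would be made with the data in hand.

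**Working it through.** **1. Trial counts.** The article's totals reproduce. PPI: 2 practice trials + 7 blocks × 6 trials = 44. SH: 2 practice trials + 20 = 22.

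**2. The two statements side by side.**
- Section 3.5.4: an outcome trial must be valid and normalized. Normalization acts on the eyelid trace, and the trace needs facial landmarks.
- Section 3.5.4.3: task engagement counts trials in which the child is not detectable in the frame.
- No detectable face means no landmarks, hence no trace and nothing to normalize. Whatever criterion the cited source sets for validity, such a trial cannot meet it. The numerator among valid trials is therefore always zero.

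**3. Task engagement under each reading.** Let T be the trials presented and k the trials with the child undetectable. Over all trials the score is k/T. Over valid trials it is 0/(T − k), taking the remaining trials as valid. The values of k are illustrative, because the article gives no rate of disengagement.

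| T | k | All trials presented | Valid trials only |
|---|---|---|---|
| 44 | 4 | 4/44 = 9.1% | 0/40 = 0% |
| 44 | 11 | 11/44 = 25.0% | 0/33 = 0% |
| 44 | 22 | 22/44 = 50.0% | 0/22 = 0% |
| 22 | 2 | 2/22 = 9.1% | 0/20 = 0% |
| 22 | 6 | 6/22 = 27.3% | 0/16 = 0% |
| 22 | 11 | 11/22 = 50.0% | 0/11 = 0% |

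The zero in the last column does not depend on k. If further trials are invalid for other reasons, the denominator shrinks but the score stays at 0%.

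**4. Head rotation, as an example of the other behaviors.** Let h be the true share of trials with rotation and q the share of those trials whose eyelid trace is invalid. Assume that trials without rotation are all valid. Among valid trials the observed share is h(1 − q)/(1 − hq). Neither h nor q is in the article, so both are assumptions shown over a range.

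| q | h = 20% | h = 40% |
|---|---|---|
| 0 | 20.0% | 40.0% |
| 25% | 0.15/0.95 = 15.8% | 0.30/0.90 = 33.3% |
| 50% | 0.10/0.90 = 11.1% | 0.20/0.80 = 25.0% |
| 75% | 0.05/0.85 = 5.9% | 0.10/0.70 = 14.3% |
| 100% | 0% | 0% |

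Under this assumption the bias is downward whenever q exceeds 0. It ranges from none to complete, and the article does not locate q.

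**The case against.** The strongest reply is that section 3.5.4.3 is the operative text and the sentence in section 3.5.4 is a loose summary. Section 3.5.4.3 speaks of data reaching beyond eyeblinks and includes vocalizations, which need no eyelid trace. An outcome defined by undetectable trials also presupposes that those trials are counted. This is a plausible account of the intent, and it stands to that extent: the article does not show a settled plan to discard those trials. It does not remove the problem, because it means the extraction sentence is wrong as written. What the camera records and which trials are used for extraction are separate matters, and the only sentence on the second names general motor behavior explicitly.

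Four stronger readings are tempting, and the article does not support them.

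- **Head movement cannot register a child who turns away.** The article does not define a valid trial. Section 3.5.4.3 also lists a vestibulo-ocular measure correlating head turns with pupil movement, which implies that some head-turn trials stay trackable. Attenuation is possible, but total loss is not shown.
- **The most disengaged children would get the best scores, or the group contrast would reverse.** If every child scores 0%, task engagement has no ordering to reverse. For the other behaviors, reversal would need strongly unequal trial loss between groups, and nothing in the article shows that.
- **Children who stop a session early are mishandled.** Whether the denominator is scheduled or presented trials, and how incomplete sessions count, is detail that an article may leave to the full protocol. The statement that "All participants retain the right to withdraw at any time without penalty" concerns leaving the study and says nothing about counting trials.
- **The variable must be renamed because a higher value means less engagement.** The label does run against the scale, but the definition is explicit, so renaming is a preference.

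It is also fair to say that the clear damage is to one behavior of ten, outside the malnutrition outcome on which the sample size rests.

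**Conclusion.** The contradiction between sections 3.5.4 and 3.5.4.3 is real and lies in stated text, so it is not a matter of omitted detail. Read as written, the extraction rule makes task engagement 0% for all children in all three groups, whatever their true value, and removes any group contrast or severity association for that outcome. This rests on one premise that the article itself supplies: an eyelid trace requires tracked facial landmarks.

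For head rotation and the other behaviors the conclusion is weaker. They would be undercounted to the extent that the behavior invalidates the trace, by an amount the article does not allow one to state. PPI, SH and the nutritional outcomes are unaffected. The correction should be made before outcomes are extracted, so that the choice of trials is not made after group data have been seen.

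**What to change.** In section 3.5.4, restrict the valid-normalized-trial rule to the measures that come from the eyelid trace: PPI, SH, the acoustic startle response and the eyelid baseline measures. In section 3.5.4.3, state that the behaviors expressed as a percentage of trials, including task engagement, are computed over all trials presented, whether or not the eyeblink trace is valid, and that the number presented is reported for each child.

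The cost is a sentence in each section and a change to the extraction script. No new data are required, because section 3.5.4.3 already provides for passive camera and microphone capture during both sessions.
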